# 2. COVID-19 CLINICAL PROFILE

Important published research studies on COVID-19 were selected to tabulate the data on symptoms (Table 1), timelines of the course of disease (Table 2), complications (Table 3) and co-morbidity (Table 4).

COVID-19 is an acute respiratory tract infection. Though the clinical phenotype is similar to influenza, the spread and severity of illness is much more in case of COVID-19. The overall mortality of COVID-19, albeit due to respiratory complications, seems to be several folds higher than that of influenza. And unlike influenza, there is no vaccine or specific drugs to kill the virus.

Viral RNA levels have been demonstrated from upper respiratory and lung specimens. In over 90% cases, the viral RNA tests on nasopharyngeal swabs was found to be repeatedly negative at about 10 days after the onset of symptoms but the viral shedding may continue well beyond clinical recovery; median duration 20 days (range of 8 to 37 days) (9,10). In mild infections, the virus may not be detected especially if the viral RNA level in respiratory specimen is less than 106 copies/mL. Some recent studies have also shown prolonged virus shedding in stool samples.

The incubation time of COVID-19 is about 5-7 days and the infectivity is often high much before the onset of symptomatic illness (11). The infection remains asymptomatic in a substantial proportion of community and a predominant proportion of symptomatic cases will suffer from mild to moderate cases. However, asymptomatic individuals may show abnormalities in the lungs on computed tomography (CT) scans (12). It is estimated that less than 20 % cases will rapidly progress to severe stage and develop life threatening lung and systemic complications requiring critical care and often life support systems like ventilators. The overall mortality rate is about 2-3%. According to the WHO, the recovery time appears to be around two weeks for mild infections and three to six weeks for severe disease.

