**SECONDARY**

1. To determine the therapeutic effect of a combination of SOC plus a selected standardized Ayurvedic drug on surrogate markers of COVID-19 disease severity and complications, and recovery pertaining to broad based domain of acute phase reactants, pro-inflammatory cytokines, imaging assessment, anti-oxidant activity, organ dysfunction and damage
2. To determine the early and late post-recovery health benefits of a combination of selected standardized Ayurvedic drug plus SOC using qualitative measure of health status (WHO Quality of life assessment questionnaire) and health related behaviour, habits and fitness questionnaire
3. To describe the clinical profile of COVID-19 with special reference to early symptoms, severity of disease, complications, course of disease, diagnostic investigations, biochemical and imaging abnormalities, patterns of recovery
4. To determine the predictors of early and late recovery from COVID-19 using a therapeutic combination of SOC plus a selected standardized Ayurvedic drug

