The total study period is 12 weeks; Primary Efficacy is ‘Clinical Recovery’ as described in the protocol; Study participant developing severe COVID 19 or severe complication and requiring special critical support/ ICU/ ventilator support will be withdrawn from the study but followed up to record outcome; Both Ayurvedic and Allopathic Physicians will jointly examine and monitor study participants in addition to the hospital treating physician.

Patients will be selected from the outpatient or inpatient facility in COVID-19 medical centres/hospitals. The study will be explained to the volunteer patients and those willing to sign the informed consent will be screened for eligibility as per the inclusion and exclusion criteria in the protocol. Patient suffering from severe COVID-19 will be excluded (see exclusion criteria below).

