# CLINICAL EVALUATION INCLUDING AYURVEDIC ASSESSMENT

Both Allopathic and Ayurvedic physicians, and predesignated study personnel will carry out assessment of all study patients as per the study schedule of events and timelines shown in Fig 1. and in Appendix A.

Several of the patient centric assessments including health and quality of life measures will be completed by the study paramedic without the knowledge of the drug allocation of the patient (assessor blind).

Standard study case record forms will be used on patient enrolment (baseline) to record patient data and will included demographics, personal habits, comprehensive medical history and examinations, measures of health and quality of life (Appendix H). The Ayurveda physician will also record the required clinical parameters of the study patient in the Ayurveda Case Record Form (Appendix I).

The routine hospital case record sheet will be used to record the patient’s progress while in hospital. The study investigator and the Ayurvedic physician will extract the relevant data of the patient from the hospital case sheet on a daily basis and enter it into the ‘study progress sheet’. (Appendix J).

On completion of treatment and at time of discharge, the investigators will complete the study completion case record form which will also include parameters on outcome (recovery or death) (Appendix K). The study patients will be provided with a precise follow-up schedule for the post treatment evaluation and during which the patients will be assessed as per schedule of events (Table 1) at weeks 4, 8 and 12 (study completion). It should be noted that some patients may require a longer period to recover that may extend from 3-4 weeks and in which case the assessment at discharge will also comply with the requirements of week-4 time endpoint (see Table 1).

During the study period, the study patient will complete a self-reported questionnaire on COVID 19 related symptoms daily which will be provided in the form of a mobile application. The self-reported questionnaire is enclosed in Appendix L.

All patients withdrawn for any reason will complete a medical examination and complete other documents as required on study completion (see above). If possible, laboratory evaluation as described above for study completion will also be done.

Laboratory and imaging investigations will be carried out as per Table 1 and are further described below.

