# 8. STUDY DURATION, FOLLOW- UP SCHEDULE AND PROCEDURES

This is summarized in Figure 1 and Table 1. There are several foot notes provided in Table 1 to further clarify a particular event/test procedure and often with particular reference to the role of the study investigator. Several of the clinical events with reference to clinical examination, study record forms and questionnaires, study procedures, laboratory diagnostics and assessments are elaborated in Appendices enclosed with the protocol (Appendix A to S).

It should be noted that this is a study treatment protocol and that the time to outcome in terms of recovery following onset of illness and/or admission to hospital is a varying parameter. The large majority of study patients are expected to recover completely but based on prior knowledge the mortality of COVID-19 in severe case in well documented (see literature review, section above). It is expected that the majority of patients will recover and be discharged to home within 5 days to 15 days of hospitalization.

However, all study patients who recover are required to follow with the study investigators on pre-determined time points as shown in Table 1.

The total duration of the study is 12 weeks and includes the duration of treatment and post clinical recovery or post-hospital discharge period to ensure optimum recovery and regain of health status.

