# 9.WITHDRAWAL AND PREMATURE TERMINATION

The patient can withdraw from the study at any point of time without assigning any reason.

The study investigator can also withdraw the patient for reasons arising out of the study drug intervention such as- intervention treatment failure, progression to severe disease, requirement of critical support care (ICU), requirement of persistent oxygen support, need for ventilation, drug related toxicity, protocol violations etc. All patients withdrawing from the study will be requested to complete the formalities (including laboratory evaluation) of study completion case record form and outcome/ hospital discharge. However, they will be encouraged to continue the clinical and other assessments enumerated for post treatment study schedule in Table 1.

There are several other reasons for patient to withdraw from the study such as:

1. Patients who worsen or need ICU admission or ventilator support due to any reason
2. Non-compliance of the treatment regimen
3. Participants not willing to continue the study
4. Drug related toxicity
5. Any serious adverse event that makes the participant unable to do the activities of daily living / any SAE
6. Any other serious medical condition which the participant may acquire during the course of the trial which makes it difficult for the participant to continue in the trial
7. Any other condition which the investigator feels might cause harm to the participant

All adverse events (AE), and in particular serious adverse event (SAE) will be dealt with as described in the section on AE (see below).

The study investigator s will be required to keep an informal contact with such a study patient uptp the study completion at 12 weeks and record post study withdrawal clinical developments. The probable outcomes of such a study patient will be stated in the case record form and include asymptomatic status, days of hospitalization, symptomatic disease and its severity, time to discharge, time to recovery, death, post recovery status as stated in the patient completion case record form and outcome report

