# 10. PATIENT POPULATION

The patients will be largely drawn from COVID-19 clinics and outpatients in various medical colleges and hospitals. All patients will be admitted in the hospital for standard care and those willing to participate in the study will be screened and enrolled as described above. Only patients with mild to moderately severe symptoms will be selected as described above. If the patients progress to a severe stage of illness as described below, they will be withdrawn from the study but the investigator will be encouraged to follow the patient ill study completion at week 12 and during this period record the hospital management, course of illness , final outcome and post recovery health status as described in this protocol.

- 1. Inclusion Criteria:

1. Typical Clinical presentation of acute onset febrile illness with cough and a RT_PCR based laboratory confirmation test for COVID-19
2. Patients with either sex, 21to 69years age
3. Patients with Mild to Moderate COVID-19 as described below
4. All patients must agree not to share medication
5. Patients willing to participate and sign an informed consent
   Note: The criteria for mild to moderate COVID-19 are based on the WHO recommendations (See Section 2.5 above with WHO Table on clinical syndromes of COVID-19 and include Mild disease and Uncomplicated Pneumonia but not severe disease which requires any form of intensive care such as invasive techniques for supplemental oxygen or ventilation and life support systems, and absence of any life threatening complications (such as severe respiratory failure, adult respiratory distress syndrome, septicaemia shock and other complications shown in Table 3 above)
   1. Exclusion Criteria

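### Secondary objective 2 asks about health after recovery, which is itself the primary outcome, and unequal follow-up plus the four-week analysis rule leave the quality-of-life comparison open to modest post-randomisation selection

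*Combined protocol and SAP*

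**What the plan says.** - **Objective.** Section 4, secondary objective 2: "To determine the early and late post-recovery health benefits of a combination of selected standardized Ayurvedic drug plus SOC", using WHOQOL-BREF and HR-BHF. It names no analysis population and no rule for patients who die, progress or do not recover. Section 11.1 makes clinical recovery (time and proportion) the primary efficacy measure.
- **Who must attend.** Section 8: "all study patients who recover are required to follow with the study investigators on pre-determined time points as shown in Table 1". The section on clinical evaluation is wider: "The study patients will be provided with a precise follow-up schedule for the post treatment evaluation", at weeks 4, 8 and 12.
- **Patients who progress.** Fig 1: they "will be withdrawn from the study but followed up to record outcome". Section 10: "they will be withdrawn from the study but the investigator will be encouraged to follow the patient ill study completion at week 12". For withdrawn patients generally, Section 9 says "they will be encouraged to continue the clinical and other assessments enumerated for post treatment study schedule in Table 1", and adds that investigators "will be required to keep an informal contact with such a study patient" until week 12. The outcomes listed for that contact do not name the questionnaires, and the completion form in Appendix K contains neither.
- **Endpoint.** Section 11.2, item 9, lists health status with no condition on recovery.
- **Analysis.** Section 17.2 plans a completer analysis and an intent-to-treat analysis with last observation carried forward. The latter is limited to patients with four weeks of intervention and the visit four weeks after enrolment.
- **Timing.** Questionnaires follow the study calendar. Under note (ii) of Appendix A, week-4 or week-8 assessments merge into discharge when discharge falls within two weeks of them.

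**The concern.** Randomisation makes the arms comparable at entry. It does not make recovered, or retained, patients comparable if the drug changes who recovers or stays. A drug that prevents progression keeps frailer patients in its own arm while their counterparts on SOC have left, and the retained drug arm then looks worse than it should.

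A second problem can run the other way. The assessments are tied to the calendar, so a drug that only shortens the illness gives its patients more convalescence by week 4. Read against objective 2, the primary effect would be reported again as a distinct benefit after recovery.

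At stake is whether this secondary comparison is between randomised groups, and whether its label matches what it measures.

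**Working it through.** **Step 1: is there a figure to reproduce?** No. Section 17.1 sets 70 per arm (2 × 70 = 140) by consensus. The documents give no effect size, SD, correlation or recovery rate by arm. The rates and correlations below are assumptions.

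**Step 2: who drops out of the analysis?** Table 2 of the protocol gives median times to ICU admission of 10.5 and 12 days (upper quartiles 17 and 15). If these are counted from onset, most patients withdrawn for progression would leave before week 4 and so fall outside the intent-to-treat set. The completer set is not defined, but it can hardly be wider.

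**Step 3: size of the selection.** Suppose a patient enters the comparison when latent health exceeds a cut-off. Quality of life has correlation ρ with latent health, and the drug raises the proportion p entering but changes no one's quality of life. With c = z(1 − p):

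- bias in SD = ρ × [φ(c_drug)/p_drug − φ(c_SOC)/p_SOC]
- SE = √(1/(70 p_drug) + 1/(70 p_SOC))

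For 80% against 90%: φ(c)/p is 0.350 on SOC and 0.195 on drug, a difference of −0.155. Multiplying by ρ = 0.3, 0.5 and 0.8 gives −0.046, −0.077 and −0.124. SE = √(1/63 + 1/56) = 0.184. A Monte Carlo check with 2 million draws at ρ = 0.5 also gave −0.077.

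| p, SOC vs drug | Bias in SD (ρ = 0.3 / 0.5 / 0.8) | SE | Chance of significant apparent harm (nominal 2.5%) |
|---|---|---|---|
| 80% vs 80% | 0 / 0 / 0 | 0.189 | 2.5% throughout |
| 80% vs 85% | −0.023 / −0.038 / −0.061 | 0.186 | 3.3 / 3.9 / 5.1% |
| 90% vs 95% | −0.026 / −0.043 / −0.069 | 0.176 | 3.5 / 4.3 / 5.9% |
| 80% vs 90% | −0.046 / −0.077 / −0.124 | 0.184 | 4.4 / 6.2 / 9.9% |
| 60% vs 80% | −0.088 / −0.147 / −0.235 | 0.204 | 6.3 / 10.7 / 21.0% |
| 70% vs 90% | −0.091 / −0.151 / −0.241 | 0.190 | 6.9 / 12.1 / 24.4% |

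For scale, the difference detectable with 80% power is (1.96 + 0.84) × √(2/70) = 0.47 SD, or 0.51 to 0.53 SD after the 15–20% withdrawal assumed in Section 17.1.

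**Step 4: what follow-up of the others does.** At 80% vs 90% and ρ = 0.5, measuring 0%, 50%, 80% or 100% of patients otherwise missing gives a bias of −0.077, −0.032, −0.011 or 0 SD.

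**Step 5: can the sign turn?** Assume scores of 70 (never at risk of progressing), 55 (progression prevented) and 45 (progressed), with the drug halving a progression risk p0 to p1.

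- All randomised: (p0 − p1) × (55 − 45) = +0.5 at 10% → 5%, and +1.0 at 20% → 10%.
- Progressors left out: (0.90 × 70 + 0.05 × 55)/0.95 − 70 = −0.79, and (0.80 × 70 + 0.10 × 55)/0.90 − 70 = −1.67.
- Same scores, with only deaths removed at the 2–3% mortality in Section 2, halved by the drug: (0.98 × 70 + 0.01 × 55)/0.99 − 70 = −0.15, and (0.97 × 70 + 0.015 × 55)/0.985 − 70 = −0.23.

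**Step 6: speed of recovery.** If recovery is 3 days faster and scores rise 0.5 to 1 point per day (both assumed), the week-4 difference is 3 × 0.5 = 1.5 to 3 × 1 = 3 points with no separate effect. The merge rule adds to this. If days are counted from enrolment near admission, a patient discharged on day 13 is scored at day 28, but one discharged on day 15 is scored at day 15. Section 8 expects most discharges at 5 to 15 days, so the boundary at day 28 − 14 = 14 lies within that range. WHOQOL-BREF looks back two weeks, so the earlier form covers the illness and the later one convalescence.

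**The case against.** The best defence is that the text is less restrictive than objective 2 suggests. A reader might infer that follow-up is required only of patients who recover. Section 8 does not say so; its sentence can be read as reminding discharged patients to return. The clinical evaluation section gives study patients in general the week 4, 8 and 12 schedule, and asks patients withdrawn for any reason to complete an examination and the end-of-study documents. Section 9 obliges investigators to stay in contact, and Section 10 includes health status after recovery in what is to be recorded for progressors who are followed. That defence stands against the word 'only'. It does not make the questionnaires mandatory at fixed weeks after withdrawal.

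A reader might also infer a planned recovered-only comparison. None is stated: item 9 of Section 11.2 is unrestricted, HR-BHF is also collected before discharge, and the population for objective 2 is simply undefined. The restriction that is explicit is the four-week rule.

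Finally, a reader might infer that an effective drug will look harmful. The reversal in Step 5 rests wholly on assumed inputs. It counts every progressor as never recovered, whereas Section 2 gives three to six weeks for recovery from severe disease. It also gives patients never at risk no gain; a gain in them of about 0.8 points (0.79 × 0.95/0.90) or 1.9 points (1.67 × 0.90/0.80) would restore a positive sign. The protocol's "less than 20 % cases will rapidly progress to severe stage" is a ceiling for cases in general, while this trial excludes severe disease and patients likely to worsen. The speed effect in Step 6 pulls in the opposite direction.

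It can fairly be said, too, that better week-4 scores through faster recovery are a legitimate part of the total effect between randomised groups. That is right. The fault there is the label and the merged visit, not the use of calendar visits.

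**Conclusion.** The concern holds as one of an undefined population and unequal follow-up. Objective 2 conditions on the primary outcome, the questionnaires are not secured for patients who progress, and the four-week rule removes most of those who leave early. The resulting selection can bias against a drug that prevents progression.

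In most scenarios tried the bias is below one standard error. It exceeds one only with a 20-point difference in recovery and ρ = 0.8. It vanishes if recovery is equal in the arms or if everyone is measured. The model assumes that the drug leaves each patient's quality of life unchanged; a true gain larger than the bias would still show as benefit.

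Separately, whatever the size of the selection, the plan as worded cannot distinguish a benefit after recovery from recovering sooner. For one secondary endpoint in an exploratory trial without a power calculation, this should be corrected but does not threaten the primary analysis. It needs settling before data collection, because questionnaires never collected cannot be recovered at analysis.

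**What to change.** 1. **Objective 2 (Section 4).** Restate it as health status at weeks 4, 8 and 12 after randomisation in all randomised patients, whether or not recovered. Do not describe the result as a benefit after recovery.
2. **Sections 8, 9 and 10.** Make the existing WHOQOL-BREF and HR-BHF at those weeks required of all randomised patients, including after withdrawal from treatment, subject to consent. It follows that a form completed at discharge should not stand in for week 4 or week 8 on these two instruments.
3. **Section 17.2.** Analyse this endpoint by randomised arm without the four-week condition. Rewording Sections 4 and 8 alone would still leave early-withdrawn patients out.
4. **Deaths.** Add a rank-based sensitivity analysis with deaths ranked lowest.

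The instruments and visits already exist. The cost is some rewording in five sections, a few more questionnaires from withdrawn patients, and slightly more analysis work.

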# 5. STUDY DESIGN

Fig 1 shows the study flow and the overview of study design and timelines, and principal study events including clinical examinations, laboratory and other investigations.

Each of the three selected and standardized Ayurveda drugs i.e. **AYUSH 64 (A-64), Sanshamani Vati Plus (SV +)** and **Yashtimadhu (MYT)** will be assessed as add on or adjunct treatment in three different drug trials of two arms each for efficacy and safety under a common current protocol.

Each of the drug trial will be a randomized, prospective, open label, parallel efficacy, active control two arm multicentre study. Each of the three Ayurveda drugs is being considered as an adjuvant drug to Standard of Care (SOC). The SOC and Ayurveda drug combination is the experimental interventional arm which will be compared to the active control arm of standalone SOC. The total duration of each of the three drugs’ study is 12 weeks and this period includes time to clinical recovery (defined later in text) and a period of follow up to complete 12 week of observation following admission to the hospital. The nature of SOC and any follow up medication will be decided by the treating physician. Some variation in SOC between different study sites and even between patients is possible. The study investigators will meticulously record the details of SOC in the study case record form of each patient. The dose of Ayurvedic drugs is as per standard Ayurveda practise and decided by consensus amongst experts in the AYUSH working group for this patient. The total sample size of each drug study is 140 patients with 70 patients randomized to each arm.

